## Statistical analysis

### Sample size

Based on primary cognitive function outcome—the SRM correct rate [5], we calculated the sample size. Sample size was determined via PASS software (PASS 15, NCSS, LLC. Kaysville, UT, USA) for a power of 0.80 and a two-tailed α level of 0.05. Parameters were derived from a prior study [5] (mean SRM correct rate at 1-month follow-up: 64.67%, SE: 3.88, SD: 15.03, dropout rate: 37.5%). Calculations yielded permissible error (δ) = 16.20 (20% of mean), and σ = 15.03. Recruitment won't exceed original participants; thus, 24 patients per group are needed. Thus, 24 patients per group are needed. Based on a 20% dropout rate, each group ended up with 30 participants.

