### Statistical methods

To assess the normality or approximate normality of the data, we will employ a combination of histograms and the Shapiro–Wilk test. For normally or approximately normally distributed data, we will report the results as mean ± standard deviation (SD). If the data exhibit skewness, we will express the results as medians and quartiles. Categorical data will be presented as absolute numbers and percentages. Appropriate statistical tests, such as t-tests, nonparametric tests, or chi-square tests, were used in assessing differences in baseline characteristics between groups.

Consideration of repeated measurement data, we employed three strategies for presentation. Firstly, a line graph was utilized to depict values (whether rates or averages) at distinct time points. Secondly, we applied mixed regression models to assess both between-group and time effects for both primary and secondary outcomes. We will employ the stepwise selection approach to construct parsimonious regression models. These adjustments will account for additional factors that may potentially influence these associations, including age, ECT sessions, HAMD-24 score, SDS score, gender, current medication usage, disease duration, etc. Age and gender were entered in all models regardless of their statistical significance. Thirdly, we examined simple effects at different time points and adjusted *p*-values to reduce the risk of false positives.

No interim analysis and subgroup analysis will be performed. Transforming the data into a longitudinal format to meet the fitting requirements of mixed regression models. The statistical analysis of our data will be conducted using SPSS version 25.0 and R version 4.1.3. We define statistical significance as a two-tailed *p*-value of less than 0.05.

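### Stepwise covariate selection in the outcome models modestly inflates type I error for the between-group effect and leaves the adjusted estimate undefined until the data are seen

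*Protocol article*

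**What the plan says.** All of the relevant text is in the protocol article, section Statistical methods.

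- Scope: "we applied mixed regression models to assess both between-group and time effects for both primary and secondary outcomes".
- How the models are built: "We will employ the stepwise selection approach to construct parsimonious regression models".
- Candidate factors: "including age, ECT sessions, HAMD-24 score, SDS score, gender, current medication usage, disease duration, etc". Seven are named and the list is left open.
- What is protected: "Age and gender were entered in all models regardless of their statistical significance". This leaves five named factors (number of ECT sessions, HAMD-24, SDS, medication, disease duration), plus whatever 'etc.' covers, to selection.
- Threshold: "We define statistical significance as a two-tailed" p-value below 0.05.
- The only p-value adjustment concerns the third strategy: "we examined simple effects at different time points and adjusted" the p-values. It addresses several time points, not model selection.

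The article gives no entry or removal criterion and does not say whether group is in the model while covariates are chosen. It names no correction for selection and no unadjusted or fixed-covariate model for the primary outcome.

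**The concern.** In a randomised comparison, covariates are there to absorb outcome variation that was foreseeable before treatment. Choosing them by their p-values in the trial's own outcome data does something else: it keeps factors that happen to correlate with the outcome in this sample. The residual variance then comes out too small, and the standard error and p-value of the group effect are computed as if no search had taken place. With about 48 completers this is not negligible.

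Two further consequences do not depend on the error rate. The adjusted tDCS effect is not defined until the data have chosen its covariates. And because selection is run per model, SRM and the secondary outcomes may end up adjusted for different factors, which makes their estimates harder to compare.

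**Working it through.** **Inputs from the article.** Sample size section: "for a power of 0.80 and a two-tailed α level of 0.05"; "Calculations yielded permissible error (δ) = 16.20 (20% of mean), and σ = 15.03"; 24 per group, raised to 30 for 20% dropout. Statistical methods: two forced covariates, five named candidates, an open list.

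**The plan's own figure.** n = 2(z₀.₉₇₅ + z₀.₈₀)²σ²/δ² = 2 × (1.960 + 0.842)² × 15.03² / 16.20² ≈ 13.5, so 14 per group; the noncentral-t version gives 15. Then 15/(1 − 0.375) = 24 and 24/(1 − 0.20) = 30. The stated 24 and 30 therefore reproduce only when a dropout allowance is applied twice. That is a separate matter. What counts here is that the analysis is planned on 24 to 30 per group, and 24 is used below.

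**Assumptions (not in the article).** Candidates are baseline values. They either carry no information, or two of them together explain 30% of the outcome variance. Entry or retention p-values range from 0.05 to 0.157. Lists longer than five stand for medication split into several indicators plus 'etc.'.

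**Simulations of the group main effect.** No true effect; group, age and gender always in the model; one outcome per subject in place of the full mixed model; group tested at nominal two-sided 0.05.

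| Selection method | Per group | Candidates | Actual type I error |
|---|---|---|---|
| Backward, 8,000 runs per setting | 24 | 5 | 5.5–6.5% |
| Backward, 8,000 runs per setting | 24 | 8 | 6.4–7.5% |
| Backward, 8,000 runs per setting | 24 | 12 | 7.3–8.6% |
| Forward–backward, 6,000 runs per setting | 24 | 5 | 5.9–6.3% |
| Forward–backward, 6,000 runs per setting | 24 | 10 | 6.2–7.5% |
| Forward–backward, 6,000 runs per setting | 30 | 5 | 5.6–6.2% |
| Forward–backward, 6,000 runs per setting | 30 | 10 | 6.2–6.9% |
| No selection, all covariates kept | 24 or 30 | 5 or 10 | 4.5–5.5%, mean 5.0% |

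Monte Carlo standard error at 6,000 runs: √(0.05 × 0.95/6000) ≈ 0.3 percentage points. Smaller checks (3,000 to 4,000 runs per setting) gave about 5–7% with five candidates and 7–8.4% with 12.

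**Mechanism.** With pure-noise candidates, mean residual variance fell to 0.97 (five candidates) and 0.87 (12 candidates, retention p 0.157) against a true 1.0. By the normal approximation the effective critical value becomes 1.96 × √0.97 ≈ 1.93 (two-sided error about 5.4%) and 1.96 × √0.87 ≈ 1.83 (about 6.8%). The too-small variance thus explains part of the excess. The rest is consistent with the group estimate itself moving when a chance-imbalanced covariate enters with an overfitted coefficient.

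**Which contrast is affected.** Write the model as y_it = group, visit and group-by-visit terms + γ′x_i + b_i + e_it, with x_i fixed per subject. In the change y_i,T1 − y_i,T0 both γ′x_i and b_i cancel. With complete data, selecting among the x_i therefore cannot move the group-by-time contrast. A repeated-measures simulation (48 subjects, 4 visits, assumed intraclass correlation 0.5, 6,000 runs per setting, 5 or 12 candidates) agrees:

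- group-by-time F test: 4.9–5.4%
- T0-to-T1 change contrast: 4.8–5.4%
- simple effect at T1: 5.3–5.7% with 5 candidates, 6.2–7.3% with 12
- group main effect: 5.4–8.3%

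**Order of selection.** If covariates are chosen without the group term and group is added afterwards, the error is 4.7–5.4% at 24 per group.

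**The case against.** Three arguments against the point deserve weight.

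*The primary outcome is a change.* The Primary outcome section defines it as the change in SRM, and the objective is faster recovery. If the test is a group-by-time contrast, selection among baseline main effects leaves it near 5%. This stands, and it rules out any claim that the 5% level is lost for every test. It does not dispose of the point. Statistical methods speaks of between-group and time effects and of simple effects, and never names an interaction. The protection also needs complete data and covariates that are constant over time. The article plans for 20% dropout and measures HAMD-24 and SDS at T0 to T3 without saying which values enter the model.

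*Covariate lists and entry rules belong in the SAP.* That holds for the missing criterion and the exact list, and neither is held against the article here. The criticism is of a method that the article states. An SAP that followed the sentence would carry the problem; one that fixed the covariates would contradict it.

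*Selection may be done without the group term.* The text does not exclude that order, and it would roughly hold 5%. The text does not require it either.

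A reader might also infer, because only age and gender are named as protected, that group itself could be dropped, so that a tDCS effect would be reported only when significant. The text does not support this. It first says that the models assess group and time effects, then describes the adjustment as covering further factors that may influence those associations, and neither group nor time is among the factors listed. Even on that reading the simulated null rejection rate is 4.6–5.1%, so it would not show type I inflation.

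**Conclusion.** The point holds and should be fixed, but its size is modest. With group in the model during selection and 24 completers per group, the type I error for the group main effect is about 5–6.5% with the five named candidates, at most about 1.5 percentage points above nominal. It is about 7–8.5% if the list grows to 12, which is an assumption. A fixed set gives about 5%. Per-visit simple effects are inflated less. A group-by-time change contrast with complete data and baseline main-effect covariates is not inflated, nor is a test after selection without the group term; the plan commits to neither.

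That the adjusted estimate depends on the selected terms holds whichever contrast is used for the group main effect or the simple effects. Different adjustment sets for SRM and the secondary outcomes are a likely result of selection, not a certain one.

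The figures rest on assumed candidate numbers, selection thresholds, covariate strength and, for the repeated-measures run, intraclass correlation.

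**What to change.** Replace the stepwise sentence with a fixed model, settled before database lock:

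- Group, visit and group-by-visit are always in the model.
- Age and gender stay in, as now.
- Add a short, named list of baseline covariates, for example number of ECT sessions (known before enrolment, since the course is complete by then) and T0 HAMD-24.
- Use the same list for every outcome, delete 'etc.', and keep all terms whatever their p-values.
- Label any stepwise model as exploratory.

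The cost is a sentence or two of text and one or two degrees of freedom for covariates that may prove uninformative. The sample size does not change.

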### Protocol amendments

Significant protocol changes will be informed to the Ethics Committee. If approved, updates will be notified in writing to involved parties, and the Chinese Clinical Trial Registry record will be adjusted.

### Dissemination policy

Before the first patient enrolls, trial details will be available on the Chinese Clinical Trial Registry. All kinds of results will be shared. They will be published and discussed in international conferences and peer-reviewed journals.

## Discussion

This is the first RCT aimed at using tDCS to assist in the recovery of CSEs caused by ECT in depression patients. Given that CSEs might hinder patients from opting for ECT [60], identifying a rehabilitation strategy could assist patients in alleviating these concerns.

Depressive patients exhibit an imbalance in cortical metabolism between the two hemispheres, with lower metabolism observed in the left frontal lobe compared to the right frontal lobe [61, 62]. ECT can induce a short-term reduction of CBF and metabolism in frontal lobe, but this alteration subsequently normalizes within around one month [13].

By utilizing the anode at left DLPFC and the cathode at right DLPFC, tDCS aims to rectify the cortical imbalance in depression, ultimately ameliorating depressive symptoms [61]. Although the mechanisms underlying the impact of tDCS on cognitive function remain not entirely clear, early research suggests that tDCS may elicit long-term effects extending beyond the stimulation period [49, 63, 64]. Otherwise, these enduring effects are likely mediated through the modulation of N-methyl-D-aspartate and gamma-aminobutyric acid receptor activity [65, 66].

Cognitively, depression in the elderly is intricately linked with dementia; past studies have suggested that depressive symptoms might be a precursor to dementia [67, 68]. Despite improvements in depressive symptoms, elderly patients often continue to exhibit deficits in visuospatial ability, information-processing speed, and delayed memory [69]. This complexity adds to the challenge of distinguishing whether cognitive deficits in elderly patients post-ECT are due to ECT itself or pre-existing conditions. Further research indicates that while ECT treatment may lead to short-term cognitive decline in elderly patients [70], there is potential for long-term cognitive improvement [71]. Therefore, enhancing cognitive function during symptom remission in elderly patients with depression is of critical clinical importance, a goal that requires further dedicated efforts [72].

There are also limitations to this RCT. Firstly, our study did not include patients over the age of 65, a demographic with a significant need for cognitive improvement. Secondly, The lack of pre-ECT cognitive assessments in our study restricted our thorough evaluation of cognitive functions in patients with depression. Thirdly, due to financial constraints as an investigator-initiated study, there is no independent Trial Steering or Monitoring Committee. However, a research management group composed of study researchers will oversee daily operations and data authenticity. Fourthly, administering tDCS in a hospital poses challenges for discharged patients in terms of transportation, potentially leading to higher drop-out rates. lastly, the research is conducted at a single site, potentially limiting the external validity of the findings.

## Data Availability

Not applicable.

## Abbreviations

CANTAB: Cambridge Neuropsychological Test Automated Battery
CBF: Cerebral blood flow
DLPFC: Dorsolateral prefrontal cortex
DSM-5: Diagnostic and Statistical Manual of Mental Disorders, Fifth Edition
ECT: Electroconvulsive therapy
HAMD-24: 24-Item Hamilton Rating Scale for Depression
MDD: Major depressive disorder
RCT: Randomized controlled trial
RVP: Rapid visual information processing
SDS: Self-rated depression scale
SRM: Spatial recognition memory
SWM: Spatial working memory
SD: Standard deviation
tDCS: Transcranial direct current stimulation
tDCS-AEQ: Transcranial direct current stimulation adverse effects questionnaire
